#### House screening

The house screening work will be undertaken by pre-trained artisans of about 4 to 5 people to be recruited from the study area. The training will be done by an in-country contractor familiar with screening of houses. The screening of 500 houses is expected to take about 2 months. Household owners will be trained on the care needed to keep the screens intact and effective and avoid activities that could result into making holes in the mesh or cause the screen to slide and create spaces that could allow mosquito entries into the houses. Other routine procedures to be used to reduce mosquito entry into houses such as closing windows and doors early will be emphasized and adherence to this practice monitored passively by the study team. As part of the intervention all the windows, doors and eaves will be screened using polyethylene material (POLYTEX INTERNATIONAL (UK) LIMITED, [name]).

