### Socio-economic data collection methods

Semi-structured questionnaire will be prepared to collect socio-demographic data at the beginning and end of the study. Each study household will be observed for durability of the screening material, the presence of holes, tears, losses and the fitness of windows and doors. The presence or absence of LLINs and the number and age of people who slept under bed nets in the previous night will be assessed in every visit to mosquito sampling (before and after screening). The impact of screening intervention on bed net use rate will be measured by observing bed net use among household members before and after house screening intervention, and between intervention and control groups. For the social science component of this impact evaluation, the team will collect data using household surveys, focus group discussions and key informant interviews. A baseline survey, midline survey and end line surveys will be undertaken using a structured household survey questionnaire and trained enumerators.

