### Entomological data analysis

Indoor and outdoor *Anopheles* densities will be compared for each study arm using a student t-test. Overall mosquito density among treatment arms will be compared using one-way analysis of variance (ANOVA) and if there is significance difference among treatment arms mean separation test will be done using turkey’s range test. The sporozoite rate will be determined as the proportion of malaria vectors positive for CSPs over the total number tested for CSPs.

The durability test of screening material will be conducted following the guideline developed by Kinde et al. (2018) [23] and modification of world health organization [48] guideline for evaluation of durability of long-lasting insecticidal mosquito nets under operational conditions. Accordingly, the durability of the screening intervention will be measured by assessing the number of holes on the meshes. Fabric integrity of all HSs fixed into windows and doors will be assessed for holes at each monitoring round. The proportion of HSs with any holes will be presented with total number of HSs in surveyed households as denominator. The scale of HS damage will be quantified using hole index formula recommended for mosquito nets and it is given as Hole index = (A x no. of size-1 holes) + (B x no. of size-2 holes) + (C x no. of size-3 holes) + (D x no. size-4 holes). Numbers 1, 2, 3, 4 refer to the size of the whole, letters A, B, C, D refer to the weight of the hole and given as 1, 23, 196 and 578 [48]. The fabric integrity of screens fixed in doors will be analysed separately as its exposure to wear and tear is higher as compared to that of windows. In depth interviews, photo-based observation will be conducted to measure community acceptance of the intervention.

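### Screen durability is measured only by holes in screens still in place, so lost, detached or slipped screens do not count against it

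*Protocol article*

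**What the plan says.** Three sections of the protocol article bear on this.

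- **Entomological data analysis** sets the measure: "the durability of the screening intervention will be measured by assessing the number of holes on the meshes". The screens inspected are those in position: "Fabric integrity of all HSs fixed into windows and doors will be assessed for holes at each monitoring round". Two summaries follow. The first is a proportion: "The proportion of HSs with any holes will be presented with total number of HSs in surveyed households as denominator". The second is a severity score: "The scale of HS damage will be quantified using hole index formula recommended for mosquito nets", where the "letters A, B, C, D refer to the weight of the hole and given as 1, 23, 196 and 578". Door screens are to be analysed apart from window screens. The section cites an earlier Ethiopian screening study and a modified WHO net-durability guideline as its basis.
- **Socio-economic data collection methods** sets a wider field observation: "Each study household will be observed for durability of the screening material, the presence of holes, tears, losses and the fitness of windows and doors".
- **House screening**, under Interventions, tells owners to avoid actions that could "cause the screen to slide and create spaces that could allow mosquito entries into the houses".

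No section says how a missing, detached or displaced screen enters either summary, or whether the denominator is screens installed or screens still present.

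**The concern.** The field observation and the analysis do not match. Losses and fit are collected as aspects of durability, and a slid screen is recognised as a way in for mosquitoes, but the two durability summaries use holes alone. A hole index devised for nets suits mesh damage. A screen fixed in a frame can also fail by coming off or by no longer sealing the opening, and these failures may leave no hole to count.

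The result would be a form of survivor bias: the screens that failed most completely contribute nothing adverse. Durability is worth getting right because the Background argues for screening over indoor spraying partly on how long screens stay intact. A hole count on surviving screens cannot by itself answer that question.

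**Working it through.** The protocol gives no durability figure to reproduce, so the check applies its stated measures to the possible states of a screen.

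**Inputs**
- Hole weights 1, 23, 196 and 578 (Entomological data analysis).
- L, the share of installed screens lost or detached: not in the document; assumed range 5–30%.
- h, the share with any hole among screens still fixed: not in the document; assumed range 10–40%.

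**Step 1: score for a single screen.** Hole index = 1·n1 + 23·n2 + 196·n3 + 578·n4.
- Slipped, mesh intact: all counts are 0, so the index is 0 and the screen is not holed.
- In place with one smallest hole: index 1, holed.
- In place with one largest hole: index 578, holed.
- Lost or detached: there is no fixed mesh to inspect. Either it is entered with no holes (index 0), or it leaves the calculation.

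So a screen that no longer seals its opening but has sound mesh scores better than one in place with a single smallest hole.

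**Step 2: proportion with any holes.**
- Reading A, lost screens stay in the denominator: reported share = h(1−L).
- Reading B, lost screens drop out: reported share = h.
- Lost screens counted as failed: share = h(1−L) + L.
- Shortfall under A: [h(1−L) + L] − h(1−L) = L.
- Shortfall under B: [h(1−L) + L] − h = L(1−h).

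**Step 3: values over the assumed ranges.**

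| h | L | Reported, A | Reported, B | Losses counted | Shortfall, A | Shortfall, B |
|---|---|---|---|---|---|---|
| 10% | 5% | 9.5% | 10% | 14.5% | 5 points | 4.5 points |
| 10% | 30% | 7% | 10% | 37% | 30 points | 27 points |
| 20% | 10% | 18% | 20% | 28% | 10 points | 8 points |
| 20% | 30% | 14% | 20% | 44% | 30 points | 24 points |
| 40% | 5% | 38% | 40% | 43% | 5 points | 3 points |
| 40% | 30% | 28% | 40% | 58% | 30 points | 18 points |

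The shortfall runs from 5 to 30 points under A and from 3 to 27 points under B. Under A the reported damage falls as losses rise: at h = 20% it goes from 18% at L = 10% to 14% at L = 30%. Slipped screens with intact mesh are not in L and would add their own share to the shortfall under both readings.

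**The case against.** The strongest reply is that the protocol does not neglect loss or fit. The data collection section plans to observe "the presence of holes, tears, losses and the fitness of windows and doors", and nothing says these observations will go unreported. The hole measures can be read as covering fabric integrity, one component of durability. The two cited guidelines are not shown and might contain a loss component, and a condensed article may leave the tabulation to a fuller document. The proportion with any holes is also correct for what it names; the share with losses counted is a different quantity.

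Much of this stands, and it limits what can be claimed. A reader might infer any of the following, but the document does not support them:

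- *Losses go unrecorded.* They are to be recorded; the gap is that the durability measures do not use them.
- *Every lost or torn-off screen is scored as undamaged.* That is certain only for a slipped screen without holes. A lost one may instead drop out, and a tear in a screen still in place may be counted as a large hole.
- *The rule ranks a house with an open doorway above one with a pinhole in a window.* There is no pooled house score, and doors are analysed separately.
- *Any one figure, such as 28% against 18–20%, is the expected error.* It rests on assumed rates.
- *The malaria results are compromised.* Durability is not among the listed objectives or endpoints.

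What does not stand is that this is merely omitted detail. After citing its guidelines, the section states that durability as a whole is measured by counting holes. That is a rule, and it is narrower than the protocol's own field observation.

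**Conclusion.** The concern holds in a limited form. Followed as written, the durability measures cannot register a lost, detached or slipped screen as a failure, so durability is overstated under either reading of the denominator. The direction is certain if any screen is lost, detached or displaced without holes, provided that such a screen is regarded as a durability failure. The protocol's own field observation and its warning about sliding screens support that view.

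The size cannot be derived from the document, because no loss rate is given. It is L or L(1−h), about 3 to 30 percentage points over the assumed ranges. The effect is confined to a descriptive measure; the malaria incidence analysis and the sample size are untouched.

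**What to change.** In Entomological data analysis:

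1. State that the denominator is all screens installed, separately for doors and for windows.
2. Report the share lost, detached or ill-fitting at each monitoring round, from the observations already planned under Socio-economic data collection methods.
3. Add one combined measure, the share not intact and in place: lost, detached, ill-fitting or with any hole.
4. Keep the hole index as a descriptor of screens still in place. No hole-index cut-off is needed; one set loosely could make the combined measure look better than the simple share with holes.

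The cost is a change of wording and a little more tabulation, with no new field observation. Reported durability may look slightly worse.

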### Social science data analysis

The socioeconomic data analysis will be done using descriptive and econometric approaches. An incremental cost effectiveness ratio (ICER) will be calculated for each outcome and arm using standard Disability Adjusted Life years (DALYs). The interventions will be ranked according to cost effectiveness, whereas inequality in terms of health outcomes, will be measured by the Gini coefficient and the concentration index.

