**Methods:**

A four-armed household, cluster-randomized, controlled study will be conducted to assess the combined impact of HS, LLINs and push-pull agricultural technology (PPT) against clinical malaria in children in Ethiopia. The unit of randomization will be the household, which includes a house and its occupants. A total of 838 households will be enrolled in this study. In this trial 246 households will receive LLINs and HS, 250 will receive LLINs, HS and PPT, 175 households will receive LLINs and PPT. The remaining 167 houses which receive LLINs only will be used as control. One child aged ≤14 years will be enrolled per household in each treatment and followed for clinical malaria using active case detection to estimate malaria incidence for two malaria transmission seasons.

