#### Specific objectives

i.To determine whether adding house screening of windows and doors of houses and implementing PPT reduces the rate of malaria parasite infection, parasite density, and anemia in children (aged between 5 to 14) compared to situations where only LLINs are used.ii.To assess whether the proposed interventions reduce human mosquito-interaction (human biting rates, mosquito resting density, longevity, sporozoite rates, and the entomological inoculation rate (EIR)) inside houses compared with LLINs alone.iii.To determine the incremental costs, benefits, and cost-effectiveness of adding house screening and PPT to usage of LLINs.iv.To assess the economic, social, and environmental feasibility of the combined intervention of house screening, LLINs and PPT.

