**Fig. 1 Fig1:**
[figure not shown]
Flow chart of the study

In this study, a total of 167, 246, 250 and 175 houses will be included in four different treatments, treatment 1 (control, LLINs only), treatment 2 (LLINs and HS), treatment 3 (LLINs, HS and PPT) and treatment 4 (LLINs and PPT), respectively. The differences in sample size across arms is due to differences in number of households within each sub-village. To full fill the total sample size, we did the random selection based on population size of each sub-village. Census of children under 14, and above 14 years of age will be made in all 838 households selected. One child will be randomly selected from each house for annual malaria parasite survey. In addition to the annual parasite screening survey, monthly follow up will be implemented in all households to monitor clinical malaria by health extension workers. If a child moves or quits the study, we will replace the child from the same house. In instances where the whole family leaves the area, we will document them as lost to follow up.

The selected children will be checked up every month for clinical symptoms of malaria infection, splenomegaly, and development of anaemia. Blood test will be conducted if the child develops clinical symptoms. The child will also be surveyed at the beginning and end of each transmission season to estimate the prevalence of *Plasmodium species* infection, parasite density, and the prevalence of anaemia. Collections will be made from both indoor and outdoor settings.

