## Discussion

Countries and inter-state actors who work in public health sectors are running out of options to contain vectors of malaria vectors as existing interventions become less effective due to growing insecticide resistance [4] and adaptive behavioral shift of vector mosquitoes to evade the interventions [50]. Thus, all options including research for novel vector control interventions [51], combination of existing strategies (e.g. combination of LLINs and IRS, [52] and supplementing them with auxiliary strategies e.g. combination of LLINs and HS, [14] are being tried as part of the ongoing research and innovation in the field of vector control. In addition, a recent modelling study conducted by Kassie et al. (2020) [53] showed that integrated interventions aimed at relaxing the constraints of multiple health problems (animal-human-plant health) are more effective in improving the overall welfare of humans as compared to the stand alone interventions. Thus, in this study we aim to test and assess the combined effect of 1) LLINs and HS 2) LLINs, HS and PPT and 3) LLINs and PPT. Households that receive LLINs alone will be used as control.

Screening houses for the purpose of excluding mosquito vectors into residential structures is well established practice in Europe [54], America [55] and some parts of tropics [5] however, these experiences were given less emphasis in Africa as main stay vector control intervention (LLINs and IRS) predominated the vector control arena. A specific design of the house (e.g. thatched roof, Iron sheet cover, closed eve, open eve) can play critical role in increasing or decreasing the odds of malaria infection [9] and mosquito density per capita or per house [36, 56,  57]. In addition to alleviating malaria, the introduction of house screening intervention in houses has resulted in reduced infection of other vector borne diseases such as dengue, leishmaniasis, yellow fever and Zika [58].

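### Ranking the arms on cost-effectiveness ratios, most naturally read as ratios to LLINs alone, can put the best package last and does not show the cost of adding PPT to HS

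*Protocol article*

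**What the plan says.** The Social science data analysis section gives the cost-effectiveness plan in two steps. The first is the ratio: "An incremental cost effectiveness ratio (ICER) will be calculated for each outcome and arm using standard Disability Adjusted Life years (DALYs". The second is the decision rule: "The interventions will be ranked according to cost effectiveness". It names no comparator for the ratios.

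The comparator has to be read from elsewhere. Specific objective iii is "To determine the incremental costs, benefits, and cost-effectiveness of adding house screening and PPT to usage of LLINs". The General objective compares the combined intervention with households that have LLINs alone. The Discussion says "we aim to test and assess the combined effect of 1) LLINs and HS 2) LLINs, HS and PPT and 3) LLINs and PPT" and names LLINs alone as the control.

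On the arms, the text under the study flow chart says "a total of 167, 246, 250 and 175 houses will be included in four different treatments": LLINs only, LLINs with HS, LLINs with HS and PPT, and LLINs with PPT.

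**The concern.** The arms are overlapping packages. LLINs sit inside every arm, and LLINs with HS sit inside the triple package. For any one household or area a programme chooses one of the four, so they are mutually exclusive.

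For such options the ratio of each package to a common control does not identify the best choice. A cheap package with a modest effect can have a lower ratio than a larger package that is worth more at the programme's threshold. The ratio of the triple package to LLINs also averages the return on HS and the return on PPT, so a poor return on the last component can be hidden by a good return on the first.

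This matters because cost-effectiveness is a specific objective, an endpoint in the abstract and the subject of a planned paper. The Conclusion offers national malaria programmes information on the interventions both combined and applied singly. They will want to know whether PPT is worth adding where houses are screened, and ratios to LLINs do not answer that.

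**Working it through.** The article states no cost, DALY, ICER or threshold, so there is no figure of its own to reproduce. The arm sizes are consistent (167 + 246 + 250 + 175 = 838) but do not enter the calculation. **All costs, effects and thresholds below are assumed**, per household and relative to LLINs alone.

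Formulas:
- Ratio to LLINs = extra cost / DALYs averted.
- Sequential ICER = difference in cost / difference in DALYs averted, against the next cheaper package still in the list.
- Net benefit = threshold × DALYs averted − extra cost.

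**Case 1: PPT has a moderate effect**

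| Package | Extra cost | DALYs averted | Ratio to LLINs | Net benefit at 12,000 |
|---|---|---|---|---|
| LLIN+HS | 50 | 0.010 | 50/0.010 = 5,000 | 120 − 50 = 70 |
| LLIN+PPT | 30 | 0.005 | 30/0.005 = 6,000 | 60 − 30 = 30 |
| LLIN+HS+PPT | 80 | 0.013 | 80/0.013 = 6,154 | 156 − 80 = 76 |

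On ratios to LLINs the order is HS, PPT, HS+PPT.

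The sequential analysis orders the packages by cost:
- LLIN to LLIN+PPT: 30/0.005 = 6,000.
- LLIN+PPT to LLIN+HS: (50 − 30)/(0.010 − 0.005) = 4,000. This step is cheaper than the one before it, so LLIN+PPT is extendedly dominated and is removed.
- LLIN to LLIN+HS: 5,000.
- LLIN+HS to LLIN+HS+PPT: (80 − 50)/(0.013 − 0.010) = 10,000.

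So LLINs alone are preferred at thresholds below 5,000, LLIN+HS from 5,000 to 10,000, and LLIN+HS+PPT above 10,000. LLIN+PPT is never preferred, yet the ratio ranking places it second. At 12,000 the ratio ranking puts the best package last. At 8,000 the net benefits are 30 (HS), 10 (PPT) and 24 (HS+PPT), so HS leads but the ratio ranking still has PPT and HS+PPT the wrong way round.

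**Case 2: PPT has a small effect**

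The costs are the same, and DALYs averted are 0.010, 0.001 and 0.011 for HS, PPT and both. The ratios to LLINs are 5,000, 30,000 and 80/0.011 = 7,273. The step from HS to HS+PPT costs 30/0.001 = 30,000. Net benefits at 12,000 are 70, 12 − 30 = −18 and 132 − 80 = 52, so the two methods give the same order. The ratio of 7,273 nevertheless conceals a last step about four times as expensive (30,000/7,273 = 4.1).

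**Case 3: strong synergy**

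The costs are the same, and DALYs averted are 0.010, 0.004 and 0.020. The ratios to LLINs are 5,000, 7,500 and 4,000. In the sequential analysis both single-component packages are extendedly dominated and HS+PPT remains at 4,000. Both methods put HS+PPT first.

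**The case against.** **The section does not say that the ratios are to LLINs.** It says incremental and leaves the comparator open, so a sequential or net-benefit ranking is not excluded. The silence is real, and the point should not be put as though the comparator were stated. The wording fits a sequential analysis poorly, however. There, dominated arms receive no ICER, and the remaining ICERs rise with cost by construction, so ranking them only repeats the cost order. An ICER for every arm followed by a ranking makes sense mainly as ratios to one control. If the authors intended something else, the text still needs to say so.

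**A condensed article leaves such detail to a fuller plan.** This holds for the threshold, the handling of dominance and the construction of DALYs, and their absence is not the complaint. The complaint is about the decision rule that the article does state.

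**The ranking need not be wrong.** This stands. Case 2 gives the same order under both methods, and Case 3 gives the same top package. The claim is that the rule can fail, not that it will.

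**ICERs are planned for each outcome, so malaria DALYs are not the whole analysis.** True, but ranking exclusive packages on ratios to a common control has the same weakness for any outcome.

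**A stronger reading is tempting.** Screening is a whole-house purchase ("As part of the intervention all the windows, doors and eaves will be screened using polyethylene material"), while clinical malaria is followed in one child ("One child aged ≤14 years will be enrolled per household in each treatment"). A reader might infer that household costs will be divided by one child's DALYs and that cost per DALY is therefore overstated. The article does not support this. It does not say whose DALYs enter the ratio or which costs are counted. The socioeconomic analysis uses a survey of 3010 households. Its listed outcomes include cost of illness per household and working days lost to malaria, and their detail is referred to a registry record not shown here. A proportional undercount in every arm would also leave the ranking unchanged.

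**Conclusion.** The concern holds for the ranking rule. Read with its objectives, the article most naturally ranks four mutually exclusive packages on ratios to LLINs alone. That rule can place an extendedly dominated package above a better one, and it does not report the cost of adding PPT to HS. In Case 1 the best package at a threshold of 12,000 comes last, and its step from HS costs 10,000 per DALY, where the ratio to LLINs shows 6,154. These figures depend entirely on assumed inputs. The conclusion also rests on reading LLINs alone as the comparator, which the analysis section does not state.

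The one-child inference is not part of the finding. It would matter only if the index child's DALYs alone were counted. In that case cost per DALY would be overstated by 1 + (household size − 1) × (benefit per other resident / benefit to the child). With assumed sizes of 4 to 6 and relative benefits of 25% to 100%, the factor runs from 1 + 3 × 0.25 = 1.75 to 1 + 5 × 1 = 6.0. It is 1.0 if other residents gain nothing.

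**What to change.** In the Social science data analysis section, name the comparator of each ICER and replace the ranking sentence by one of two rules:

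- **Full incremental analysis:** order the four arms by cost, remove dominated and extendedly dominated arms, and report each remaining arm's ICER against the next cheaper remaining arm. Where both HS arms remain and are adjacent, this gives the cost of adding PPT to HS directly.
- **Net monetary benefit:** rank the four arms on net benefit over a stated range of thresholds, with the uncertainty of that ranking.

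Ratios to LLINs alone can stay as a description, without a ranking. It would also help to add one sentence on whose DALYs are counted. If child results are extended to other residents, that assumption should be shown with a range.

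The change needs no new arm and no data beyond the costs and outcomes already planned. Its price is a little more analysis and the need to state and defend a threshold range.
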